# Effectiveness of the secondary distribution of HIV self-testing with and without monetary incentives among men who have sex with men living with HIV in China: study protocol for a randomized controlled trial

**DOI:** 10.1186/s12879-023-08062-w

**Published:** 2023-03-14

**Keywords:** HIV self-testing, People living with HIV, Men who have sex with men, Monetary incentives, Secondary distribution

## Abstract

**Background:**

The HIV epidemic is still expanding among men who have sex with men (MSM) in China, but HIV testing rates remain suboptimal. Network-based interventions, such as secondary distribution, have shown promise to expand HIV self-testing (HIVST) among partners of MSM living with HIV (MLWH) but have not been widely implemented. Monetary incentives could enhance the secondary distribution of HIVST in some settings. We will conduct a randomized controlled trial to examine the effectiveness of monetary incentives in expanding the secondary distribution of HIVST among MLWH in China.

**Methods:**

We will recruit 200 eligible participants at three antiretroviral therapy (ART) clinics in China. Participants are eligible if they are 18 years of age or over, assigned as male at birth, have had anal sex with men, are living with HIV, are willing to apply for the HIVST kit at ART clinics, and are willing to provide personal contact information for follow-up. Eligible participants will be randomly assigned in a 1:1 ratio to one of two groups: standard secondary distribution group and secondary distribution group with monetary incentives. Participants (defined as “index”) will distribute the HIVST kits to members of their social network (defined as “alter”) and will be required to complete a baseline survey and a 3-month follow-up survey. All alters will be encouraged to report their testing results by taking photos of used kits and completing an online survey. The primary study outcomes will compare the mean number of alters and newly-tested alters motivated by each index participant in each group. Secondary study outcomes will include the mean number of alters who tested positive, the cost per person tested, and the cost per HIV diagnosed for each group.

**Discussion:**

Few studies have evaluated interventions to enhance the implementation of secondary distribution. Our study will provide information on the effectiveness of monetary incentives in expanding HIVST secondary distribution among MLWH. The findings of this trial will contribute to implementing HIVST secondary distribution services among MLWH in China and facilitating HIV case identifications.

**Trial registration:**

Chinese Clinical Trial Registry ChiCTR2200064517; http://www.chictr.org.cn/showproj.aspx?proj=177896. Registered on 10th October 2022.

## Background

Key populations account for less than 5% of the global population, but they and their sexual partners comprised 70% of new HIV infections in 2021 [1]. In China, the HIV prevalence among MSM was 5.4% by 2021, but only 59% of MSM knew their HIV status [2]. Although traditional facility-based HIV testing services have expanded HIV testing among MSM in China, additional strategies are still needed to improve HIV testing coverage among MSM [3–6].

HIV self-testing (HIVST) complements traditional facility-based HIV testing services and has been recommended by the World Health Organization (WHO) and other HIV testing service guidelines [7, 8]. HIVST has participants collect their own samples, perform the test, and read the results themselves [9]. It is a convenient, rapid, and discrete HIV testing strategy. Moreover, HIVST can identify and link additional people with HIV to care, effectively improving the detection rate and expanding HIV testing coverage in MSM [10, 11]. Therefore, HIVST is gradually being promoted as an HIV testing strategy to expand HIV testing services for key populations. Among the HIVST distribution strategies, secondary distribution is an innovative method that is one of the most promising in promoting HIV testing among people in the social network of the index key populations [12, 13]. Studies have shown that this model has the potential to be a new measure of HIV prevention and control in MSM populations, serving the dual purpose of promoting first HIV testing and detecting positive infections [14–16].

People living with HIV (PLWH) are vital in ongoing HIV transmission, and their behavioral characteristics determine the rate and extent of HIV transmission [17]. MSM have large sexual networks, and there is evidence that the proportion of MLWH infected by casual or regular partners has been increasing in recent decades [18]. HIVST may help to expand HIV testing services among sexual partners of MLWH. PLWH can serve as a source of intervention by encouraging their sexual partners to get tested. A pilot study conducted in Vietnam showed that it is feasible and effective to facilitate HIV testing by assisting PLWH in contacting their sexual partners and providing free HIVST kits [19].

Secondary distribution of HIVST kits among social networks of MLWH, especially among sexual partners, may improve HIV testing coverage. However, some barriers remain. Psychological and behavioral economic theories suggest that individuals prefer the “present”: over-valuing the present and severely under-valuing the future [20, 21]. This implies that information alone may not be sufficient to change behavior when there are direct costs and delayed benefits to a behavior. As in the case of HIVST, there are direct logistical and psychological costs, while the benefits of HIVST become apparent later [22]. Using monetary incentives can increase direct benefits, offset current costs, and spur behavior change. There is growing evidence that monetary incentives, particularly fixed monetary incentives and conditional cash transfers, increase the demand for and acceptance of HIV testing [23–26]. Moreover, few studies have explored the effects of monetary incentives to use HIVST among sexual partners in MLWH. Further research is urgently needed to fill the current gap, which could also be used to complement studies exploring the cost or cost-effectiveness of secondary distribution strategies in PLWH.

In this study, we propose to explore the effectiveness of the secondary distribution of HIVST with and without monetary incentives among MLWH through a randomized controlled trial in Zhuhai, China.

### Objectives

The primary objective of our trial is to evaluate the effectiveness of the monetary incentives in expanding the secondary distribution of HIVST among MLWH.

### Hypotheses

We hypothesized secondary distribution with monetary incentives would be more effective in expanding the secondary distribution of HIVST among MLWH and would identify more MSM living with HIV but not aware of their infection status.

## Methods/design

### Trial design

The study is a randomized controlled trial in which MLWH who meet the recruitment criteria are randomized into two groups: standard secondary distribution group and secondary distribution with monetary incentives group. All enrolled MLWH will be offered several HIVST kits in ART clinics. Participants will complete the baseline survey at the start of the trial and the corresponding alter will complete the online survey when the HIVST results are returned (Fig. 1).

**Fig. 1 Fig1:**
[figure not shown]
Trial Flowchart

### Study setting and recruitment

Building on existing research [16, 27], the Social Entrepreneurship to Spur Health (SESH) research team, the Zhuhai Center for Disease Control and Prevention (CDC), and the Zhuhai Xutong Volunteer Service Center (Xutong), an MSM-friendly community-based organization (CBO), will further strengthen their collaboration to pinpoint the target population from MSM to MLWH. The MLWH will be recruited in Zhuhai through an online ordering system developed by Xutong, which is managed on WeChat, the largest social networking platform in China.

The study will be conducted at three ART clinics in Zhuhai: two designated hospital clinics of Zhuhai CDC (The Fifth Affiliated Hospital of Sun Yat-sen University and The Fifth Affiliated Hospital of Zunyi Medical University) and Xutong community health service station (Lingnan Community Health Service Station). These clinics and their services are selected for the study because they are developed with input for MSM and provide “one-stop” services. More specifically, the “one-stop” service is a platform for HIV-screening providers to give all service referrals for screen-positive patients at designated ART hospitals, which offer specialized medical services, including consultation, epidemiological investigation, follow-up, HIV confirmatory sample delivery, and antiretroviral therapy. All clinics are staffed by MSM peer volunteers, nurses, and public health staff. Study recruitment will be conducted face-to-face with MLWH at these three sites, where researchers will fully introduce the specifics of the project to MLWH and invite them to participate in the study after a scientific introduction on how to use the HIVST kits by themselves.

### Eligibility criteria

Participants are eligible for inclusion only if they met all of the following inclusion criteria: (1) be assigned male gender at birth; (2) at least 18 years or older; (3) ever had anal sex with men; (4) living with HIV; (5) willing to apply for HIVST kits at ART clinics; (6) willing to provide personal contact information for follow-up.

### Randomization and allocation

A biostatistician who is not involved in participant enrollment will produce and keep computer-generated randomization codes. Eligible MLWH participants will be electronically randomized individually and independently to the intervention and control groups through a computer-generated procedure based exclusively on a 1:1 allocation ratio. At the site, index participants will be asked to randomly select a random code via a computer-generated electronic program after the baseline survey. The researcher will group participants according to the random code.

### Interventions

We will randomly assign participants to either the standard secondary distribution group as the control group or the secondary distribution with the monetary incentives group as the intervention group. All enrolled MLWH will receive HIV self-test kits at the ART clinics.

### Standard secondary distribution group/ control group

MLWH assigned to this group will serve as the index participants in this group for the secondary distribution of HIVST. They will complete a baseline survey and apply for up to 5 HIVST kits as needed, paying a deposit based on the number of HIVST kits claimed (0.01RMB deposit per kit). Setting up a deposit is to verify the WeChat account, thus facilitating the issuance of subsequent incentives and obtaining contact information for follow-up visits to ensure results return. Each HIVST kit will be packaged in an unmarked box to protect privacy, in addition to the HIVST instructions and a “return card” included inside the box. The return card contains a QR code that allows testers to anonymously and privately scan and upload a photo of their test results to the online platform. The return card also contains a confirmation number to identify the different index participants and their corresponding alters. After receiving the HIVST kit, MLWH index participants will distribute it to their sexual partners, friends, or others in their social network. The alters accepting the self-test kits and returning the results will be considered a successful distribution.

### Secondary distribution with monetary incentives group/ intervention group

MLWH in this group will follow the same process as the control group. The difference is that when an alter accepts the HIVST kit and returns the result, both the index who distributed to the alter and the alter himself/herself will receive a bonus reward of 30 RMB (≈ 4 USD) as monetary incentives. All incentives will be provided through online trading. Within this group, index participants can distribute up to 5 alters and obtain incentives of up to 150 RMB.

### Consultation, follow-up, and referral services

Research staff will provide face-to-face counseling or online counseling before and after the test. On-site, trained research staff, will provide pre-test consultation to all participants and fully inform them how to use HIVST kits in person when they apply for a test kit. In addition, each HIVST kit will also include instructions. Post-test consultation for those who upload HIV-negative results will include a reminder of what the test result means and how to prevent HIV infection. Individuals with “positive” or “inconclusive” test results will be contacted immediately via phone or WeChat. Individuals with positive self-test results will be offered post-test consultation services, including a detailed explanation of test results and timely referrals to clinics for confirmatory tests. In addition, researchers will encourage positive testers to pass on the HIVST kit to their sexual partners or provide contact information for their sexual partners, who researchers will contact to provide free testing services.

### Study measures

For the baseline survey, index participants who meet the inclusion criteria will complete the baseline questionnaire. We will collect socio-demographic characteristics (age, gender, marital status, the highest level of education completed, and monthly income), sexual behavior (previous sex, role during sex with men, condom use, number of sexual partners, and drug use), influence within personal social circles, previous HIV testing experience and their social network.

After three months, we will follow up with the index MLWH, asking them about the distribution process, focusing on their experience and attitude in distributing the self-test kits and their willingness to recommend them. In addition, when alters upload their results, they will also be required to complete a questionnaire online. We will ask about their socio-demographic characteristics, sexual behavior, the experience of previous HIV testing, experiences and attitudes toward using HIVST kits, and their social network.

Participants are required to collect their fingertip blood samples according to the instructions for use. All blood samples will be analyzed using the SD Bioline HIV/Syphilis duo test kits (SD Bioline, Company, South Korea). The trained staff at CBO will examine the resulting photographs and provide corresponding post-test consultation, which will be recorded in the JINSHUJU.

### Outcomes

Our primary outcome will be (1) the mean number of alters motivated by each index in each group, which will be compared between the two groups; (2) the mean number of newly tested alters motivated by each index in each group. Secondary outcomes will be (1) the mean number of alters who tested positive for HIV recruited by index participants in each group; (2) the cost per person tested and HIV diagnosed for each group.

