### Sample size

Based on the results of the pilot study and related studies, the number of alters motivated by the index through standard secondary distribution was set at 0.65, and through the secondary distribution with monetary incentives, was set at 1.0, assuming equal variance between the two groups, we used a standard deviation of 0.5 for all groups [16, 27]. We set the required sample size at 100 people, for a total of 200 people, with an alpha of 0.05, a power of 0.90, and a lost follow-up rate of 0.20.

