### Data analysis

All statistical analyses will follow the intention-to-treat principle. We will use descriptive analysis to report baseline characteristics. For baseline differences between index participants who completed the 3-month follow-up survey and those who did not, we will use a two-sample t-test for comparison if the data are normally distributed and a chi-square test if not. A p-value less than 0.05 is considered statistically significant.

Considering the distribution of the results and based on related studies, we will use zero-inflated negative binomial regression for the primary outcome analysis [27, 28]. The primary outcome analysis will compare the differences between the control and intervention groups. Then the incidence rate ratio (IRR) and its associated 95% CI will be estimated further to compare the primary outcome difference between the two groups. For the secondary outcome analysis, we will compare differences in the mean number of alters who tested positive for HIV recruited by index participants in each group and further assessed by IRR and its associated 95% CI. In addition, we will also apply logistic regression for the secondary outcome analysis. We will perform a subgroup analysis of the first primary outcome, stratified by statistically significant factors. All IRRs will be adjusted by index participant-related factors.

If possible, we will conduct an economic evaluation by using micro-costs to assess the total cost per group, the cost per person tested and the cost per HIV diagnosed for each group. Also, we will compare the cost-effectiveness in the two groups, intervention and control groups.

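### Two primary outcomes share a single 0.05 threshold with no stated order, split or joint rule; if either can carry the claim, the false-positive rate exceeds 5% (at most 9.75%)

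*Protocol article*

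**What the plan says.** The Outcomes section lists two items under the primary label. The first is "the mean number of alters motivated by each index in each group, which will be compared between the two groups"; the second is "the mean number of newly tested alters motivated by each index in each group". The abstract confirms that both are to be compared: "The primary study outcomes will compare the mean number of alters and newly-tested alters motivated by each index participant in each group".

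The Data analysis section gives one threshold: "A p-value less than 0.05 is considered statistically significant". For the primary analysis it specifies zero-inflated negative binomial regression and adds: "Then the incidence rate ratio (IRR) and its associated 95% CI will be estimated further to compare the primary outcome difference between the two groups". It says nothing about an order of testing, a split of alpha, or a need for both outcomes to be significant. The only wording that resembles a ranking is "We will perform a subgroup analysis of the first primary outcome, stratified by statistically significant factors", which says which outcome receives the subgroup analysis, not which is tested first.

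The Sample size section uses the number of alters alone: "the number of alters motivated by the index through standard secondary distribution was set at 0.65". Against this it assumes a mean of 1.0 in the incentive group, with a standard deviation of 0.5, alpha 0.05, power 0.90 and 20% loss. It gives no rate or effect for newly tested alters.

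**The concern.** Two tests at 0.05 give two chances of a false-positive primary result. The Objectives and Hypotheses sections speak of effectiveness in expanding secondary distribution without saying which outcome decides the question. A reader of the published plan could therefore accept a significant result on either outcome as primary success, and the 0.05 in the sample-size statement would not be the error rate of that claim.

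A second, distinct matter is that a positive headline could rest on newly tested alters, an outcome for which the plan gives no assumed rate, effect or power.

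**Working it through.** **Inputs from the protocol article.** Means 0.65 and 1.0 (difference 0.35), standard deviation 0.5, alpha 0.05, power 0.90, loss 20%, 100 per arm. Two-sided testing is assumed, because sidedness is not stated and 95% intervals are used.

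**Inputs assumed.** The share q of alters who are newly tested (30 to 70%) and the dispersion of the counts (Poisson, or negative binomial with dispersion 1). The article gives neither, nor a correlation between the outcomes.

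**1. The plan's own figure.** n per arm = 2 × (1.960 + 1.282)² × 0.5² / 0.35² = 42.9, so 43. Allowing for loss, 43 / 0.80 = 53.75, so 54 per arm and 108 in total. The stated 100 per arm is not reproduced. That is a separate matter, but on these inputs the first outcome has ample room: 80 evaluable per arm give 99.3% power. The calculation contains nothing on the second outcome.

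**2. Upper bound on the false-positive rate.** Two independent tests at 0.05, either sufficing: 1 − 0.95² = 9.75%.

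**3. Allowing for the overlap.** Under both null hypotheses, take the two test statistics as bivariate normal with correlation ρ and find the probability that at least one exceeds 1.96 in absolute value:

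| ρ | 0 | 0.5 | 0.7 | 0.8 | 0.9 | 0.95 | 0.99 |
|---|---|---|---|---|---|---|---|
| At least one rejection | 9.75% | 9.07% | 8.35% | 7.81% | 7.04% | 6.46% | 5.66% |

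**4. Which ρ is plausible.** Suppose each alter is newly tested independently with probability q. For Poisson counts ρ = √q. For negative binomial counts with mean μ and dispersion a, let V = μ + aμ² and V_q = qμ + aq²μ²; then ρ = qV / √(V × V_q). With μ = 0.65:

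| q | Poisson: ρ, rate | Dispersion 1: ρ, rate |
|---|---|---|
| 0.3 | 0.548, 8.93% | 0.644, 8.59% |
| 0.5 | 0.707, 8.31% | 0.789, 7.87% |
| 0.7 | 0.837, 7.56% | 0.891, 7.12% |

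Simulation agrees. With 20,000 null trials per setting, 100 per arm, mean 0.8 and counts capped at 5, the rates for q = 0.3, 0.5 and 0.7 were 8.8%, 8.5% and 7.8% (Poisson) and 8.8%, 7.9% and 7.3% (dispersion 1).

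**5. If both outcomes had to be significant,** the rate would be at most 5%.

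**6. Power, as a separate question.** Assume the planned ratio 1.0 / 0.65 = 1.54 holds for both outcomes, with 100 per arm. The standard error of the log rate ratio is √[(1/m₀ + 1/m₁ + 2a)/100], where m₀ and m₁ are the arm means, and power is Φ(log 1.54 / SE − 1.96).

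| Outcome | Poisson | Dispersion 1 |
|---|---|---|
| Alters (0.65 v 1.0) | 77% | 52% |
| Newly tested, q = 0.5 (0.325 v 0.5) | 48% | 37% |
| Newly tested, q = 0.3 (0.195 v 0.3) | 32% | 26% |

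For example, for q = 0.5 and Poisson counts: SE = √[(3.077 + 2)/100] = 0.225, 0.431 / 0.225 = 1.91, and Φ(1.91 − 1.96) = 48%. The first row matters: replacing the standard deviation of 0.5 by a count variance also takes the first outcome from above 90% to 77% or 52%. Only part of the second outcome's shortfall comes from its smaller counts.

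**The case against.** The strongest objection is that this is an argument from silence. The document is a condensed article, multiplicity rules are often left to an analysis plan, and an order or correction may exist there. That possibility stands. But the article itself fixes two primary outcomes, one threshold and unadjusted 95% intervals, and spends its alpha of 0.05 on one outcome. Which outcome carries the primary claim is a design decision, and following the text as published lets either one carry it.

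Three stronger readings are tempting and are not supported.

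- A reader might infer that the trial's false-positive rate simply is 7 to 9%. That needs success on either outcome to suffice, which the article does not state, and a newly tested share that it does not give.
- A reader might infer that leaving the second outcome out of the sample size raises the false-positive rate. It does not; it affects power only.
- A reader might take the first outcome as securely powered and the second as the only weak one. The first is well powered only on the Sample size section's own inputs. Under the count variances used to show low power for the second, it also falls below 90%.

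It is also fair to say that the 0.05 sentence closes the paragraph on baseline comparisons. Applying it to the primary tests is an inference, though a reasonable one given the alpha of 0.05 in the sample size and the 95% intervals.

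**Conclusion.** The point holds in conditional form, as a change that should be made and not as a flaw that invalidates the trial. Two primary outcomes are named without a rule linking them. If either may carry the claim, the familywise false-positive rate is above 5% and at most 9.75%. It is about 7 to 9% for newly tested shares of 30 to 70%, with share and dispersion assumed and the correlation following from them. It approaches 5% only as nearly all alters become newly tested. Separately, no power is established for newly tested alters. The power figures above are illustrative, since they rest on an assumed share, an assumed variance and the same rate ratio for both outcomes.

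**What to change.** State a fixed sequence in the order in which the Outcomes section already lists the outcomes. Test the number of alters per index at two-sided 0.05. Test newly tested alters confirmatorily at two-sided 0.05 only if the first test is significant; otherwise report the second as an estimate with its confidence interval. This holds the familywise rate at 5%, leaves the full 0.05 on the outcome used for the sample size, and needs no extra participants. If an unpublished analysis plan already contains a rule, state it alongside the outcomes.

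The downside is that newly tested alters cannot support a confirmatory claim if the first test fails. If an independent claim on that outcome is wanted, testing each at 0.025 is an alternative, with a familywise rate of at most 1 − 0.975² = 4.94%. On the plan's own inputs the first outcome then needs 51 per arm, or 64 after 20% loss, and 80 evaluable per arm give 98.6% power. With Poisson variance and 100 per arm, its power would fall from 77% to 68%.

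The cost is one sentence. The Trial status section says that statistical analysis had not begun, so the rule could still be set before the data are analysed.

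### The HIV-positive secondary outcome is not limited to previously undiagnosed alters, so it does not measure the new case finding in the hypothesis

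*Protocol article*

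**What the plan says.** The Outcomes section of the Protocol article gives the first secondary outcome as "the mean number of alters who tested positive for HIV recruited by index participants in each group". The abstract and the Data analysis section describe it in the same terms. None of the three places restricts it to new, previously undiagnosed or confirmed infections. The Outcomes section does apply a restriction of that kind elsewhere: the second primary outcome is limited to newly tested alters.

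The Hypotheses section says that distribution with incentives "would identify more MSM living with HIV but not aware of their infection status", and the Discussion speaks of identifying new HIV-positive cases. The second secondary outcome includes a cost per HIV diagnosis, but the article does not say what counts as diagnosed.

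Under Eligibility criteria every index participant is living with HIV. In the control-group section, whose process the incentive arm also follows, "MLWH index participants will distribute it to their sexual partners, friends, or others in their social network"; no recipient is excluded because of HIV status. The return card in each kit "allows testers to anonymously and privately scan and upload a photo of their test results". In the incentive arm only, index and alter each receive 30 RMB when a result is returned. Positive testers are contacted and offered "timely referrals to clinics for confirmatory tests", but confirmation is not part of the outcome.

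**The concern.** The outcome that should carry the case-finding half of the hypothesis counts a wider group than the hypothesis names. This matters more here than in a trial whose index participants are men of any HIV status: the networks are those of men living with HIV, so some partners and friends may already know that they are positive. If such an alter tests positive and uploads the photo, he adds one to the outcome although no infection has been found.

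Two things are at stake. First, the number of cases found would be overstated, and the cost per diagnosis understated if its denominator follows the same count. Second, because only one arm is paid per returned result, the share of non-new positives could differ between arms and distort the incidence rate ratio. Anonymous photo return, with no stated check on who tested, also leaves room for an index participant's own test to be uploaded as an alter's.

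**Working it through.** **What the plan gives.** The article states no expected number of positives, so there is no figure of its own to reproduce. The check is how many events the outcome will rest on and how sensitive it is to non-new positives.

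**Inputs.**
- Index participants: 100 per arm (Sample size).
- Alters per index: 0.65 control, 1.0 incentive (Sample size).
- HIV prevalence among alters: not given. The Background gives 5.4% for men who have sex with men in China. I assume 5.4%, 10% and 15%, since contacts of men living with HIV may differ from that population.
- Share of positives already aware, *k*: not given. The Background says 59% of these men knew their HIV status. That figure is not specific to positives, so using it for *k* is an assumption.

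**Step 1: expected positives.** Positives = index participants × alters per index × prevalence.

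| Prevalence (assumed) | Control | Incentive | Ratio |
|---|---|---|---|
| 5.4% | 100 × 0.65 × 0.054 = 3.51 | 100 × 1.0 × 0.054 = 5.40 | 1.54 |
| 10% | 6.5 | 10 | 1.54 |
| 15% | 9.75 | 15 | 1.54 |

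The total is 8.9 to 24.75 positives over both arms.

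**Step 2: previously unaware positives.** These are positives × (1 − *k*). With *k* = 0.59 the 5.4% row becomes 3.51 × 0.41 = 1.44 versus 5.40 × 0.41 = 2.21, and the 15% row 4.00 versus 6.15.

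**Step 3: *k* equal in both arms.** The factor (1 − *k*) cancels and the ratio stays at 1.54. The number of cases is overstated by 1/(1 − *k*): 1.0 at *k* = 0 and 1/0.41 = 2.4 at *k* = 0.59. If all self-test positives form the cost denominator, the cost per new diagnosis is understated by the same factor.

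**Step 4: *k* different between arms.** The observed ratio equals the true ratio × (1 − *k* control)/(1 − *k* incentive). The documents give no basis for the size of a difference, so I show the effect of one further non-new positive in the incentive arm, beyond those already inside the assumed prevalence:
- 5.4%: (5.40 + 1)/3.51 = 1.82
- 10%: (10 + 1)/6.5 = 1.69
- 15%: (15 + 1)/9.75 = 1.64

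Holding that arm's cost fixed, its cost per positive is multiplied by 5.40/6.40 = 0.84 at 5.4% and by 15/16 = 0.94 at 15%.

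**The case against.** **A reader might infer that the outcome counts the index participant's own test.** It does not. The abstract defines an alter as a member of the index's social network, so an index test is not an alter result. What remains is possible misattribution, of unknown frequency. There are partial safeguards: a confirmation number on the card, staff who examine each photo, a required alter questionnaire, and individual contact with every positive tester. None is a stated identity check.

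**A reader might infer that cost per diagnosis is defined on any positive self-test.** The article does not say so. It uses different words for the two outcomes and refers positives for confirmation, so diagnosed may mean confirmed. The term is undefined, not wrong, and the economic evaluation is planned only if possible.

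**A reader might infer that false positives are rewarded in the incentive arm.** The payment is for any returned result, with no premium for a positive one, and known-positive contacts can receive kits in either arm. Step 3 shows that if this happens equally in both arms the ratio is unaffected. A difference between arms is possible but not shown.

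**The alter questionnaire could already separate known positives.** It asks about previous testing, and details of its use may sit in a document not shown. But the article does state this outcome, in three places, without the limit that its hypothesis needs.

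**The narrower outcome is sparser.** That stands; Step 2 shows it.

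**Conclusion.** The point holds as a mismatch between a stated secondary outcome and the hypothesis it serves. As written, already-known positives would count as case finding. The number of cases would be overstated by an unknown factor: up to about 2.4 if 59% of positive alters already knew, and not at all if none did. The ratio is biased only if the share of non-new positives differs between arms. The one-arm payment makes that possible but does not establish it. Because only about 9 to 25 positives are expected in all, each additional non-new positive in the incentive arm adds roughly 0.10 to 0.28 to the ratio (1/9.75 to 1/3.51).

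These sizes rest on assumed prevalence and awareness among alters and on the planned means. The primary outcomes are not touched by this point. It should be corrected, but it does not threaten the trial's main comparison.

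**What to change.** Define the case-finding outcome as *the number of alters per index participant with a positive self-test and no HIV diagnosis before using the kit*, and use the same definition for the HIV-diagnosed cost denominator.

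- Add one item on previous HIV diagnosis to the alter questionnaire, beside its existing questions on previous testing.
- Check the answer at the contact already made with every positive tester. Use the same contact to establish that the tester is not the index participant.
- Apply both steps identically in the two arms.
- Report all self-test positives, and the number confirmed after referral, as separate descriptive lines. Confirmation should not be a condition of the outcome: that would mix attendance at a clinic into case finding and thin an already small count.

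The cost is one survey item and a short addition to an existing call. The downsides are fewer counted events and reliance on self-reported diagnosis. Recruitment was under way when the article was written, so alters who uploaded before the change will lack the item. Where the recorded consultation does not settle their status, show them as unknown.
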